### **7.9. Other Secondary Outcomes**

Secondary outcomes assessed up to 12 months will be analyzed using linear regression models adjusted for baseline values. Treatment effects will be reported as mean differences with corresponding 95% confidence intervals. If a patient does not have a 12-month outcome assessment, an alternative measurement obtained during the study follow-up will be used. Patients with no measurements for a given variable during follow-up will be excluded from that specific analysis. **Table 2** provides a proposed summary of the secondary outcome effects.

**Table 2.** Comparative Analysis of Secondary Outcomes by Treatment Group

| Secondary Outcomes                                  | Biventricular Pacing
[control] | Conduction System
Pacing
[intervention] | Effect
Measure | Effect
[95% CI] | p-value |
|-----------------------------------------------------|-----------------------------------|-----------------------------------------------|-------------------|--------------------|---------|
| Echocardiographic Outcomes                   |                                   |                                               |                   |                    |         |
| Ejection fraction (%)                               | xx.x (xx.x)                       | xx.x (xx.x)                                   | Mean dif.         | x.xx [x.xx - x.xx] | x.xxx   |
| End-diastolic volume (ml)                           | xx.x (xx.x)                       | xx.x (xx.x)                                   | Mean dif.         | x.xx [x.xx - x.xx] | x.xxx   |
| Electrocardiographic and laboratory outcomes |                                   |                                               |                   |                    |         |
| Change in QRS duration (ms)                         | xx.x (xx.x)                       | xx.x (xx.x)                                   | Mean dif.         | x.xx [x.xx - x.xx] | x.xxx   |
| BNP (pg/ml)                                         | xx.x (xx.x)                       | xx.x (xx.x)                                   | Mean dif.         | x.xx [x.xx - x.xx] | x.xxx   |
| NT-proBNP (pg/ml)                                   | xx.x (xx.x)                       | xx.x (xx.x)                                   | Mean dif.         | x.xx [x.xx - x.xx] | x.xxx   |
| Quality of life and functional capacity      |                                   |                                               |                   |                    |         |
| 6MWT distance (m)                                   | xx.x (xx.x)                       | xx.x (xx.x)                                   | Mean dif.         | x.xx [x.xx - x.xx] | x.xxx   |
| NIHA class                                          |                                   |                                               |                   |                    |         |
| I                                                   | xx.x (xx.x)                       | xx.x (xx.x)                                   | Mean dif.         | x.xx [x.xx - x.xx] | x.xxx   |
| II                                                  | xx.x (xx.x)                       | xx.x (xx.x)                                   | Mean dif.         | x.xx [x.xx - x.xx] | x.xxx   |
| III                                                 | xx.x (xx.x)                       | xx.x (xx.x)                                   | Mean dif.         | x.xx [x.xx - x.xx] | x.xxx   |
| IV                                                  | xx.x (xx.x)                       | xx.x (xx.x)                                   | Mean dif.         | x.xx [x.xx - x.xx] | x.xxx   |
| KCCQ-OSS                                            | xx.x (xx.x)                       | xx.x (xx.x)                                   | Mean dif.         | x.xx [x.xx - x.xx] | x.xxx   |
| EQ5D                                                | xx.x (xx.x)                       | xx.x (xx.x)                                   | Mean dif.         | x.xx [x.xx - x.xx] | x.xxx   |

### 7.10. Sensitivity Analyses

The primary endpoint includes, as part of the main analysis, imputation of LVEF values for patients without echocardiographic assessments during follow-up. As a first sensitivity analysis, the ordinal logistic model will be re-estimated including only patients with complete data.

As a second sensitivity analysis, the model will be refitted using the raw change in LVEF without categorization into predefined bands—that is, modeling discrete unit changes (e.g., -10%, -11%, -12%, -13%, etc.).

Additionally, to assess the robustness related to hospitalization and urgent visits for heart failure events, the total number of events during follow-up will be analyzed as count data using Poisson regression with a log-link function. These models will be adjusted for total follow-up time and the same covariates used in the Cox model. Results will be presented as rate ratios with 95% confidence intervals.

Finally, all primary and secondary efficacy analyses will also be conducted using the per-protocol (PP) and as-treated populations.

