#### 7.5.2. *Time to Death, Heart Failure Hospitalization, or Urgent HF Visit*

The composite outcome comprising the primary endpoint components (all-cause death, heart failure hospitalization, and urgent heart failure visits) will be analyzed as time to first event using Cox proportional hazards models. Results will be reported as hazard ratios (HRs) with corresponding 95% confidence intervals. Kaplan-Meier estimates will be used to display unadjusted time-to-event curves. All models will incorporate a random effect for participating site (frailty model) and will be adjusted for baseline left ventricular ejection fraction, sex, and age.

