## APPENDIX A

Four power simulations were conducted using 10,000 iterations each, assuming a total sample size of 180 patients (90 per group) and odds ratio non-inferiority margins of 1.0, 1.1, 1.2, and 1.3.

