### *Parameters*

- Alpha (two-sided) 0.05
- Primary ordinal outcome: all-cause mortality at 12 months, heart failure hospitalization at 12 months, urgent heart failure visits at 12 months, and change in left ventricular ejection fraction (LVEF) at 12 months from baseline (categorized in 5% increments)
- Expected event rates (assuming independence)
- Mortality 6.24% in both groups
- Heart failure hospitalization 5.85% in both groups
- Urgent heart failure visits 0.5% in both groups
- Mean LVEF improvement 16% in the CSP group vs 13% in the BVP group
- Standard deviation of LVEF improvement 6.5
- 5% loss to follow-up

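### The Poisson analysis of total heart failure hospitalizations and urgent visits makes no allowance for overdispersion, so its rate-ratio intervals will be too narrow if events cluster within patients (minor)

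*Combined protocol and SAP*

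**What the plan says.** Section 7.10 adds a count analysis "to assess the robustness related to hospitalization and urgent visits for heart failure events". The method is that "the total number of events during follow-up will be analyzed as count data using Poisson regression with a log-link function". Two sentences complete it: "These models will be adjusted for total follow-up time and the same covariates used in the Cox model", and "Results will be presented as rate ratios with 95% confidence intervals".

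The Cox covariates (Section 7.5.2) are baseline LVEF, sex and age. The Cox models also carry a site frailty. Section 7.10 carries over the covariates but does not say whether the site effect comes with them.

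Neither Section 7.10 nor any other section names an overdispersion check, a scale parameter, a sandwich variance, a negative binomial model or a patient-level random effect. The text also does not say whether follow-up time is an offset or a covariate.

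**The concern.** A Poisson model takes the variance of each patient's count to equal its mean. HF admissions tend to recur in the same patients, and when they do the variance is larger. The model-based standard error is then too small, and the 95% interval covers less often than stated. A site effect would not repair this, because the repetition is within patients.

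This is the only clinical-event model in the plan that uses repeat events. The primary ordinal outcome places each patient in one category, and the Cox model stops at the first event. The variance assumption therefore fails in the very situation where this analysis adds information. At stake is a robustness check that could show a difference, or a precision, that the data do not support.

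**Working it through.** **Planning inputs.** The documents give no figure for the count analysis, so there is none to reproduce. The inputs borrowed from Appendix A were checked against its power figure. An unadjusted proportional odds simulation (3,000 repetitions, margin 1.2) gave 80.5% power with 170 analysed and 82.4% with 172, against 81.4% stated. The inputs are sound, although this does not bear on the count model itself.

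**Inputs for the check.** From Appendix A: 90 per group, two-sided alpha 0.05, HF hospitalization 5.85%, urgent visits 0.5%, deaths 6.24%, loss 5%. Adding the two event rates without overlap gives p = 6.35% with an event, or 0.0635 × 180 ≈ 11 patients. The between-patient gamma variance k is an assumption, shown as a range.

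**Formulas.** Let counts be gamma-Poisson with mean m and gamma variance k.

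- With p fixed, m = [(1 − p)^(−k) − 1]/k. For k = 5: (0.9365^(−5) − 1)/5 = (1.388 − 1)/5 = 0.0776.
- Variance/mean = 1 + k·m. For k = 5: 1 + 5 × 0.0776 = 1.39.
- True-to-Poisson standard error ratio = √(1 + k·m). For k = 5: √1.39 = 1.18. The interval is then 1 − 1/1.18 ≈ 15% too narrow.

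**Simulation at the planning event proportion.** True rate ratio 1, 90 per arm, 20,000 repetitions, no covariates. About 0.5% of repetitions, those with an arm free of events, were set aside. Error is 100% minus coverage.

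| k (assumed) | Events per affected patient | Variance/mean | SE ratio | Poisson error | Robust error | Quasi-Poisson error |
|---|---|---|---|---|---|---|
| 0 | 1.03 | 1.00 | 1.00 | 2.4% | 2.4% | 2.7% |
| 2 | 1.10 | 1.14 | 1.07 | 3.9% | 3.2% | 2.8% |
| 5 | 1.22 | 1.39 | 1.18 | 6.6% | 4.5% | 3.0% |
| 10 | 1.46 | 1.93 | 1.39 | 12.4% | 5.9% | 3.0% |
| 15 | 1.76 | 2.68 | 1.64 | 20.1% | 7.6% | 3.1% |

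A repeat at k = 15 gave 19.6%, so 19 to 20% is the fair figure. With so few events the Poisson test starts below 5%, which absorbs mild clustering.

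**Higher event rates (assumed).** With 86 per arm, Poisson error at k = 0, 2 and 5 was 4.1%, 6.8% and 10.5% at a mean of 0.12 events per patient, and 4.3%, 8.8% and 15.1% at 0.20. Repeat runs agreed to within about half a point. In such runs quasi-Poisson error stayed below 5% and robust error did not exceed about 6%.

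**Does the handling of follow-up time matter for width?** Follow-up was shortened at random in 6.24% + 5% = 11.24% of 180 patients, uniformly over 0.02 to 1 year (3,000 repetitions). Coverage of the Poisson interval with a log offset and with a linear covariate was:

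- p = 6.35%, k = 0: 98.0% and 97.9%
- p = 6.35%, k = 5: 94.3% and 94.1%
- p = 15% (assumed), k = 5: 82.8% and 82.8%

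The choice does not drive the width. These figures come from a numerically stabilised fit. About 0.1124 × 180 ≈ 20.2 patients have shortened follow-up averaging 0.51 year, so they contribute about 20.2 × 0.51 × 0.0656 ≈ 0.68 events at k = 0. The chance of none is exp(−0.68) ≈ 0.51. In that case a covariate's coefficient has no finite estimate and a standard routine may not converge. This is a practical reason to prefer the offset.

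**The case against.** The strongest reply is that the trial's own rates leave little room for harm. At 6.35% with an event, error is at or near nominal for k up to 5. The larger figures need either stronger clustering or event rates two to three times those planned. This stands: inflation of 7% to 15% at k between 2 and 5 belongs to assumed means of 0.12 to 0.20, and the documents do not support it at the planning rates.

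A reader might also infer that the plan enters follow-up time as a covariate, that the result is therefore not a rate ratio, and that this narrows the intervals. The documents do not support that. The wording fits an offset equally well, and the promise of rate ratios points towards one. Follow-up is close to constant at 12 months, with events counted only to one year and 20 days (Section 7.14), and coverage was the same either way.

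Third, the analysis feeds no decision rule and has no row in Table 1. This also stands and limits the severity. It does not answer the core point, since nothing in the plan protects the interval if repeat events occur.

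**Conclusion.** The point holds as a minor one. Section 7.10 specifies plain Poisson regression for counts that can repeat within patients, with no allowance for extra variance, so the intervals will be too narrow if events cluster. The size depends on a dispersion that the documents do not give. At the planning rates the problem is negligible with about 1.1 events per affected patient, slight at about 1.2, and clear at about 1.5 or more.

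It would be wrong to read this as a threat to the trial's conclusion. The primary proportional odds analysis and its non-inferiority test do not use this model. The treatment of follow-up time is an ambiguity in wording, separate from the variance problem.

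**What to change.** In Section 7.10, before the analysis is run:

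- Keep the Poisson log-link model and name one variance in advance, either quasi-Poisson or robust (sandwich). Negative binomial regression is an alternative if event numbers allow; with about 11 affected patients expected, its dispersion would be poorly estimated.
- State that log(follow-up time) enters as an offset.
- State whether the site effect is carried over from the Cox model.

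The cost is a sentence or two in the SAP and one changed model call, with no effect on design, sample size or data collection. Intervals widen where clustering is present. With few events the robust variance can remain slightly anti-conservative (about 6% to 8% error under strong clustering), while quasi-Poisson is conservative (about 3% at the planning rates).

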### 7.11. Subgroup Analyses

The primary ordinal outcome will be assessed within predefined subgroups in the mITT population by including interaction terms between treatment assignment and each subgroup variable in the same mixed-effects ordinal logistic regression model used for the primary analysis.

Treatment effects will be reported as conditional proportional odds ratios within each subgroup level, along with corresponding 95% confidence intervals. No adjustment for multiple comparisons will be applied. The following subgroups will be evaluated:

1. Age:  $\geq$  vs.  $<$  median
2. Sex: male vs. female
3. Operator experience:  $\geq$  vs.  $<$  40 procedures performed before trial initiation
4. Baseline QRS duration:  $\geq$  vs.  $<$  median
5. Baseline LVEF:  $\geq$  vs.  $<$  median
6. Indexed end-diastolic volume:  $\geq$  vs.  $<$  median
7. Heart failure etiology: ischemic vs. non-ischemic
8. Atrial fibrillation vs. other rhythm

### 7.12. Functional Capacity Sub-study

#### *Cardiopulmonary Exercise Testing*

Cardiopulmonary exercise test (CPET) outcomes up to 12 months will be analyzed using linear regression models adjusted for baseline values. Effects will be reported as mean differences between treatment groups with corresponding 95% confidence intervals.

If the CPET is not performed at the 12-month visit, an alternative assessment obtained during the follow-up period will be used. If no follow-up measurement of the variable is available, the patient will be excluded from the corresponding analysis.

### **7.13. Missing Data**

Imputation strategies for the primary and secondary efficacy endpoints are defined within their respective analysis sections. For other exploratory outcomes, minimal missing data are anticipated given the study's structured procedures, which include site staff training and independent data monitoring.

Nevertheless, the coordinating center will contact the site investigators to obtain any missing data variables. Analyses for primary and secondary outcomes will be performed based on participants with available outcome data (i.e., available case analysis), except for the specific imputation approaches already outlined for the primary endpoint, the economic secondary endpoint, and the ordinal secondary endpoint as detailed in the Outcomes Analysis section.

### **7.14. Additional Definitions**

For the assessment of clinical outcomes, any hospitalization during which the patient undergoes heart transplantation will be classified as a heart failure hospitalization. For endpoints not involving clinical outcomes (i.e., death, hospitalization, or urgent visit for heart failure) or costs, patients who undergo heart transplantation will be censored on the date of transplantation.

Clinical outcomes (i.e., death, hospitalization, or urgent visit for heart failure) occurring after the last day of the final scheduled follow-up period (i.e., one year and 20 days after the index procedure) will not be counted. However, all other outcomes will be considered even if the 12-month visit takes place beyond the protocol-defined window.

### **7.15. Statistical Software**

All analyses will be conducted using R software version 4.4.1 (or later) (R Development Core Team, Vienna, Austria, [www.r-project.org](http://www.r-project.org)).

## APPENDIX A

Four power simulations were conducted using 10,000 iterations each, assuming a total sample size of 180 patients (90 per group) and odds ratio non-inferiority margins of 1.0, 1.1, 1.2, and 1.3.

### *Parameters*

- Alpha (two-sided) 0.05
- Primary ordinal outcome: all-cause mortality at 12 months, heart failure hospitalization at 12 months, urgent heart failure visits at 12 months, and change in left ventricular ejection fraction (LVEF) at 12 months from baseline (categorized in 5% increments)
- Expected event rates (assuming independence)
- Mortality 6.24% in both groups
- Heart failure hospitalization 5.85% in both groups
- Urgent heart failure visits 0.5% in both groups
- Mean LVEF improvement 16% in the CSP group vs 13% in the BVP group
- Standard deviation of LVEF improvement 6.5
- 5% loss to follow-up

### *Estimated power under different non-inferiority margins*

Non-inferiority margin OR < 1.0: 57.8%

Non-inferiority margin OR < 1.1: 71.3%

Non-inferiority margin OR < 1.2: 81.4% (this was the pre-specified non-inferiority margin for the primary outcome)

Non-inferiority margin OR < 1.3: 88.3%

[figure not shown]

This *Statistical Analysis Plan* (SAP) was developed prior to the initiation of study analyses, with the aim of standardizing procedures related to the execution, processing, and reporting of statistical data, ensuring consistency and transparency in the conduct of the analyses.

[[name]]

[[name]]

[[name]]
